### Methods for additional analyses (e.g., subgroup analyses) {20b}

Detection of progressive RNFL thinning and VF sensitivity decline has been shown to be more difficult in moderate to advanced glaucoma compared with early glaucoma. Subgroup analysis will be performed to determine if the rates of change of RNFL thickness and VF sensitivity would be different between treatment groups in patients with early glaucoma versus those with moderate to advanced glaucoma. Subgroup analysis will also be performed to investigate if the responses of NR supplementation would be different between old and young patients.

### Methods in analysis to handle protocol non-adherence and any statistical methods to handle missing data {20c}

Data will be analyzed on an intention-to-treat basis to include all patients who receive the randomized treatment and have at least two follow-up visits. Multiple imputation by chained equations (MICE) algorithm will be applied for estimation of missing data [28].

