## Trial design {8}

This study is a double-blind, parallel-group (1:1), randomized, controlled, superiority trial. The trial will randomize 125 patients with primary open-angle glaucoma (POAG) with evidence of progressive RNFL thinning or ganglion cell inner plexiform layer (GCIPL) thinning in optical coherence tomography (OCT) without visual field (VF) progression in at least one eye to receive oral NR 300 mg/day or placebo. Patients will be followed up at 1 month, 4 months, and then every 2 months until 24 months for comparisons of the rates of RNFL thinning and the rates of change of VF sensitivity between treatment groups. The same IOP-lowering regimen as prescribed before study recruitment will be provided throughout the 24-month study period unless a safety endpoint (described below) is reached. Change in VF sensitivity at 1 month will be compared between treatment groups to investigate neuroenhancement. We hypothesize that patients treated with NR have a slower rate of RNFL thinning and a slower rate of VF sensitivity decline compared with those treated with placebo over 24 months and that an improvement in VF sensitivity could be detected in the NR-treated group at 1 month. The study flow chart is shown in Fig. 1.

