### Criteria for discontinuing or modifying allocated interventions {11b}

The safety endpoints are (1) development of VF progression (likely progression in GPA according to the EMGT criteria) [21], (2) decrease in visual acuity ≥2 lines, and (3) IOP > 30 mmHg on 2 consecutive visits. Patients will exit the study and receive appropriate treatment if any of the safety endpoints is reached. Patients are allowed to withdraw from the study for any reasons at any time.

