## Assignment of interventions: allocation

### Sequence generation {16a}

Patients will be randomly allocated (1:1) at the baseline visit to receive NR or placebo within 1 month of enrollment. Randomization with minimization by age (< 60 years vs ≥60 years), gender (male vs female), VF MD (<−6 dB vs ≥ −6 dB), spherical equivalent (<−6.0D vs ≥ −6.0D), mean IOP measurement over the past 3 years (≤21 mmHg vs > 21 mmHg), and number of glaucoma medications (0, 1, 2, 3, or ≥ 4) will be performed using an open-source computer program MinimPy [24]. A random element was introduced in the minimization procedure (i.e., weighted randomization of 0.8) to make the randomization more unpredictable [25]. If both eyes are eligible for inclusion, the one with smaller VF MD will be selected for randomization with minimization.

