### Procedure for unblinding if needed {17b}

The blinding will be maintained until a serious adverse event occurs. Unblinded participants will exit the trial and the ocular and/or medical conditions will be managed accordingly. The management results will be recorded on the clinical report form and reported to the Hong Kong Hospital Authority Cluster Research Ethics Committee.

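### The set labelled intention-to-treat is a modified one: it requires treatment received and two follow-up visits, which needlessly conditions the 1-month visual field comparison and can drop early exits from the Cox analyses

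*Protocol article*

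**What the plan says.** The section on non-adherence and missing data {20c} labels the analysis intention-to-treat and, in the same sentence, defines the set to "include all patients who receive the randomized treatment and have at least two follow-up visits". It continues: "Multiple imputation by chained equations (MICE) algorithm will be applied for estimation of missing data". The wording covers the data in general, and no other section gives a different set for any outcome.

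Four other sections determine how the rule works in practice:

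- Sequence generation {16a}: "Patients will be randomly allocated (1:1) at the baseline visit to receive NR or placebo within 1 month of enrollment".
- Trial design {8}: "Patients will be followed up at 1 month, 4 months, and then every 2 months until 24 months". The same section adds a 1-month outcome: "Change in VF sensitivity at 1 month will be compared between treatment groups to investigate neuroenhancement".
- Criteria for discontinuing {11b}, after listing visual field progression, loss of visual acuity and raised IOP as safety endpoints: "Patients will exit the study and receive appropriate treatment if any of the safety endpoints is reached".
- Procedure for unblinding {17b}: "Unblinded participants will exit the trial and the ocular and/or medical conditions will be managed accordingly".

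**The concern.** Intention-to-treat keeps every randomised patient in the allocated arm. The set in {20c} instead selects on two events that follow allocation, and both can depend on treatment or outcome through intolerance, early worsening or a serious adverse event.

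Three things are at stake. A report that follows the plan would claim intention-to-treat for an analysis that is not. Patients with usable data would be discarded, most plainly for the 1-month outcome. And the exit rules in {11b} and {17b}, combined with {20c}, could turn an early outcome-related exit into a deletion rather than an event or a censored observation. The multiple imputation planned in {20c} does not help as written, because it does not reach patients already outside the set.

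**Working it through.** **Who is excluded.** Randomisation is at baseline, and the scheduled follow-up visits are months 1, 4, 6 and so on to 24. Two attended follow-up visits therefore require at least one at month 4 or later. A patient who attends only month 1, or no follow-up visit, is out. So is a patient who did not receive the allocated treatment; the text does not define receipt, and taking no capsules is the natural reading.

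**1-month visual field outcome.** The assessment section {18a} schedules three visual field tests at baseline and three at month 1. A patient who completes all six and then leaves has everything this comparison needs, yet is dropped.

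**Time-to-event outcomes.** The three safety endpoints differ:

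- *IOP above 30 mmHg on two consecutive visits.* Entry requires IOP of 28 mmHg or less {10}, so this normally needs two follow-up visits. The patient is already inside the set.
- *Visual acuity loss of two lines or more.* This can be met at month 1. The patient exits with one follow-up visit and is deleted instead of being censored.
- *Likely visual field progression.* This needs three consecutive tests (visual field section), and three are taken at month 1. If same-visit tests count as consecutive, which the article does not say, the endpoint could be met at month 1. The patient would then exit and leave the Cox analysis of that same event. The secondary outcome {12} also counts possible progression, which needs only two consecutive tests.

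An exit at the second attended follow-up visit or later does not trigger exclusion.

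**Primary slope: the plan's own figure first.** Inputs from the sample size section {14}: slope variance 1.39 (μm/year)², residual variance 3.83 μm², difference 0.7 μm/year, power 80%, alpha 5% (taken as two-sided). There are 19 measurements, at months 0 (×3), 1 (×3), 4, 6, …, 22 and 24 (×3).

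- Σ(t − t̄)² = 10.689 years²
- Variance of one patient's slope = 1.39 + 3.83/10.689 = 1.748
- n per arm = 2 × (1.960 + 0.842)² × 1.748 / 0.7² = 56.0, matching the stated 56
- Total = 112/0.9 = 124.4, rounded up to 125, as stated

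The sample size is not in dispute.

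**Illustrative shift.** If a fraction q of one arm is excluded and its mean slope is worse than that of the retained patients by d, the full-arm mean differs from the retained mean by q × d. Take d as one slope SD, √1.39 = 1.18 μm/year (assumption). The article gives no early-loss rate. Spreading its 10% default evenly over 24 months (assumption) gives 10% × 4/24 = 1.7% by month 4; 5% is a pessimistic case. The standard error of the difference, with 62.5 randomised per arm and one arm reduced by q, is about 0.24 μm/year.

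| q, one arm only | shift, μm/year | share of 0.7 | shift / SE | two-sided type I error |
|---|---|---|---|---|
| 1.7% | 0.020 | 3% | 0.08 | 5.1% |
| 5% | 0.059 | 8% | 0.25 | 5.7% |

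Losses that are equal in both arms, with similar slopes, cancel.

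**How much the fix recovers.** A patient with three scans at baseline and three at month 1 has Σ(t − t̄)² = 6 × (1/24)² = 0.0104. The slope variance is 1.39 + 3.83/0.0104 = 369, against 1.748 for a completer. The weight is 1.748/369, about 0.5% of a completer's. A patient with no follow-up scan adds no slope information.

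**The case against.** The strongest defence is that the inclusion rule is stated openly, so any reader can see that it is a modified set, and that few patients should fall foul of it. The trial is double-blind with identical capsules, reminders are sent before visits, and missed appointments are rearranged within two weeks. The 10% default allowance covers the whole 24 months, whereas the rule catches only losses before the second follow-up visit. The weight calculation also shows that any distortion of the primary slope is mainly the cost of early dropout itself: under missing-at-random assumptions, the mixed model and multiple imputation would largely fill in early leavers from those who stayed.

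All of that stands for the primary outcome. It does not answer the label, the extra attendance condition on the 1-month outcome, or the deletion of an early exit from the Cox analyses.

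A reader might infer more: that the primary randomised comparison is seriously compromised. The document does not support this. Losing 10% of one arm under the same assumptions would give q × d = 0.118 μm/year, 17% of the target, but that spends the full 24-month default allowance before month 4 and in one arm only. A reader might also infer that all three safety endpoints feed the exclusion; the IOP criterion normally cannot, and exits from the second follow-up visit onward are retained.

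**Conclusion.** The point holds as one of definition and label. The set in {20c} is modified intention-to-treat, selected on events after randomisation, and nothing else in the article corrects it. The certain consequence is an unnecessary later-attendance condition on the 1-month visual field comparison. The possible one is loss of an early exit from the time-to-event analyses, including a visual field event if same-visit tests count as consecutive. The frequency of such exits is not given.

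For the primary RNFL slope, the bias cannot be sized from the document and is probably small: 0.02 to 0.06 μm/year if 1.7% to 5% of one arm only is excluded with slopes one SD worse than the rest, and near zero if early losses are few and balanced. This should be fixed; it is not grounds for rejecting the primary analysis.

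**What to change.** Replace the population sentence in {20c} with wording such as:

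> All randomised patients are analysed in the arm to which they were randomised, with no minimum number of doses or visits. The mixed models use all available measurements. The 1-month visual field comparison includes all patients with month-1 data, with the others handled by the planned multiple imputation. The Cox analyses include all randomised patients from baseline, censored at last assessment if no event has occurred.

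Keep the present set as a sensitivity analysis labelled modified intention-to-treat. The cost is a short text change, made before unblinding. It needs no new data, leaves the target of 125 patients unchanged and does not touch the exit rules.

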### Plans to give access to the full protocol, participant-level data, and statistical code {31c}

No later than 3 years after the completion of data collection, the protocol and deidentified dataset will be available from the principal investigator upon reasonable request.

## Oversight and monitoring

### Composition of the coordinating center and trial steering committee {5d}

The coordinating center is located at the University of Hong Kong Glaucoma and Optic Nerve Diagnostic Center. The trial steering committee is directed by the principal investigator and includes two independent researchers and one statistician, who are not part of the same institution as any of the members of the study team. The trial steering committee is responsible to ensure the protocol is implemented as planned, review study progress on a regular basis, and uphold good clinical practice at all times. The coinvestigators, research assistants, and technicians of the trial will be responsible for all aspects of the logistics and organization of the trial.

### Composition of the data monitoring committee, its role, and reporting structure {21a}

An independent data monitoring committee comprises two independent experts in statistics, who are not part of the same institution as any of the members of the study team. They will be responsible to inspect clinical data collected during the study period, review interim analysis, and report back to the investigators if any action is required.

### Adverse event reporting and harms {22}

Adverse events will be checked by the investigators at every follow-up visit (i.e., every 2 months). Any adverse event, whether they are related to the study or not, will be recorded in the adverse effect report form provided by the Hong Kong Hospital Authority using standard adverse event language. A serious adverse event will be reported to the Hong Kong Hospital Authority Research Ethics Committee within 24 h of the event. The principal investigator will be responsible to follow the management of the serious adverse event until resolution or conclusion. The investigators and the trial steering committee will determine whether an adverse event or serious adverse event is related to the study drug.

### Frequency and plans for auditing trial conduct {23}

A team of clinical research coordinators independent of the investigators will monitor that the data reported in the clinical research forms are complete and accurate, ensure all adverse events and serious adverse events are recorded and reported, and confirm study drugs to be stored and distributed according to the good clinical practice every 3 months.

### Plans for communicating important protocol amendments to relevant parties (e.g., trial participants, ethical committees) {25}

Any amendment to the protocol will be submitted by the principal investigator to be approved by the Hong Kong Hospital Authority Research Ethics Committee and Hong Kong Food and Health Bureau Research Secretariat before implementation.

## Dissemination plans {31a}

Trial results will be presented at international scientific conferences and published in peer-reviewed scientific journals.

## Discussion

Glaucoma neuroprotection trials have been relied on event analysis of VF results for evaluation of treatment outcome, which may take 4 to 5 years to complete [4, 29]. We engineered various designs into the study to enable the detection of a potential treatment effect in 2 years. These include the adoption of (A) a structural (i.e., progressive RNFL thinning) instead of a functional biomarker (e.g., VF progression) as the primary outcome measure, (B) a clustered paradigm to collect multiple measurements at the beginning and at the end of the trial [30], (C) a frequent follow-up schedule at 2-month intervals, and (D) a trend analysis instead of an event analysis to compare the change in RNFL thickness between treatment groups [31], as well as (E) the enrollment of progressing (i.e., eyes with progressive RNFL/GCIPL thinning evident in GPA/TPA) instead of stable glaucoma patients.

Daily NR intake at 300 mg/day is considered to be safe because 300 mg/kg/day represents the no-observed-adverse-effect-level [14]. Whereas many ongoing clinical trials investigate NR at a dosage of ≥1000 mg/day, we prescribe NR at 300 mg/day because oral administration of NR at 300 mg has been shown to attain similar levels of NAD elevation in the blood at 24 h compared with oral administration of NR at 1000 mg in healthy volunteers [6].

Lowering the IOP is currently the only treatment option for glaucoma patients. Our clinical trial has the potential to demonstrate the feasibility of neuroprotection in glaucoma, which is pivotal to prevent or slow glaucoma blindness in patients with progressive loss in vision despite adequate control of IOP.

## Trial status

Study recruitment started on 9 March 2020, and the recruitment completion date is 8 March 2021. Protocol version 5 (8 Nov 2020).

## Abbreviations

EMGT: Early manifest glaucoma trial
FDR: False discovery rate
GCIPL: Ganglion cell inner plexiform layer
GPA: Guided Progression Analysis
IOP: Intraocular pressure
NAD: Nicotinamide adenine dinucleotide
NR: Nicotinamide riboside
OCT: Optical coherence tomography
POAG: Primary open-angle glaucoma
RNFL: Retinal nerve fiber layer
SITA: Swedish interactive thresholding algorithm
TPA: Trend-based Progression Analysis
VF: Visual field
